### 3 OBJECTIVES, ENDPOINTS, AND HYPOTHESIS OF THE STUDY

#### 3.1 OBJECTIVES

##### 3.1.1 PRIMARY OBJECTIVE OF THE CORE STUDY PERIOD

The primary objective of this study is to evaluate whether treatment with eight weekly subcutaneous injections of daratumumab is associated with a significant reduction of pathogenic serum anti-dsDNA antibodies in patients with moderate to severe SLE.

##### 3.1.2 SECONDARY OBJECTIVES OF THE CORE STUDY PERIOD

Secondary objectives of the study include:

1. Assessment of safety and tolerability
2. Evaluating the effect of daratumumab on SLE serology
3. Investigating the effect of daratumumab on SLE clinical endpoints and glucocorticoid sparing
4. Analyzing health-related quality of life

### 3.1.3 ADDITIONAL OBJECTIVES OF THE CORE STUDY PERIOD

1. Investigate pharmacodynamic markers (e.g. number and phenotype of peripheral plasmablasts/plasma cells, NK cells, T and/or B cell subsets, including their expression levels of CD38, type-I interferon activity), gene expression analysis and receptor repertoire changes in T and B cells
2. Investigate study drug concentration in serum (only if primary endpoint is achieved)

### 3.1.4 PRIMARY OBJECTIVE OF THE LTE OBSERVATIONAL PERIOD

1. To evaluate of the long-term safety of daratumumab, previously administered in the core study period, for the treatment of SLE

### 3.1.5 SECONDARY OBJECTIVES OF THE LTE OBSERVATIONAL PERIOD

1. To evaluate the long-term efficacy of daratumumab, previously administered in the core study period, for the treatment of SLE by means of SLEDAI-scores, CLASI scores, CDAI scores, SELENA-SLEDAI Flare Index (SFI) and attainment of SRI-4 or LLDAS responses
2. To investigate the long-term serologic changes of anti-dsDNA antibodies and other autoantibodies present at baseline of the core study, and total immunoglobulin levels in serum
3. To assess the long-term health outcome measures (SF-36, FACIT scores)
4. To investigate the damage accrual according to SLICC Damage Index (SDI)

### 3.1.6 ADDITIONAL OBJECTIVES OF THE LTE OBSERVATIONAL PERIOD

1. Investigate pharmacodynamic markers (e.g. number and phenotype of peripheral plasmablasts/plasma cells, NK cells, T and/or B cell subsets, including their expression levels of CD38, type-I interferon activity), gene expression analysis and receptor repertoire changes in T and B cells

## 3.2 ENDPOINTS

### 3.2.1 PRIMARY ENDPOINT OF THE CORE STUDY PERIOD

The primary endpoint is the reduction of serum anti-dsDNA antibody titers after 8 repeated weekly injections of daratumumab at Week 12, i.e. 4 weeks after the last daratumumab injection, compared to baseline.

### 3.2.2 PRIMARY ENDPOINT OF THE LTE OBSERVATIONAL PERIOD

1. Safety will be investigated by reporting the proportion of participants with treatment emergent adverse events (TEAE) by severity and SAEs through EOS. Routine safety evaluations include AE monitoring, physical examinations, vital sign measurements, ECGs, and clinical laboratory testing (hematology, chemistry, and urinalysis) as a measure of safety and tolerability for the entire study duration. Time frame: each visit.

### 3.2.3 SECONDARY ENDPOINTS OF THE CORE STUDY AND LTE OBSERVATIONAL PERIOD

1. Safety will be investigated by reporting the proportion of participants with treatment emergent adverse events (TEAE) by severity and SAEs through EOS. Routine safety evaluations include AE monitoring, physical examinations, vital sign measurements, ECGs, and clinical laboratory testing

(hematology, chemistry, and urinalysis) as a measure of safety and tolerability for the entire study duration. Time frame: each visit.

SAEs will be assessed at any dose that results in a death, inpatient hospitalization or prolongation of existing hospitalization, persistent or significant disability/incapacity, or a congenital anomaly. The following areas of safety interest will be routinely assessed to identify any major safety findings related to immunosuppression or potential risks associated with the individual classes of therapy:

- serious and/or opportunistic infections, herpes zoster, active TB, malignancies (all types), adjudicated gastrointestinal (GI) perforations, adjudicated cardiovascular events (e.g., major adverse cardiovascular event [MACE]), anemia, neutropenia, lymphopenia, renal dysfunction, hepatic disorders, and adjudicated embolic and thromboembolic events (non-cardiac, non-central nervous system [CNS]) including venous thrombotic events defined as pulmonary embolism and deep vein thrombosis and clinical laboratory testing (hematology, chemistry, and urinalysis) as a measure of safety and tolerability for the entire study duration.

2. To investigate the effect of daratumumab on serologic changes, the following secondary endpoints are defined:

- Change from baseline in serum levels of anti-dsDNA antibodies, immunoglobulins (IgM, IgG and IgA), antinuclear antibodies (ANA) and extractable antinuclear antibodies (ENA), such as anti-Smith, anti-Ro (SSA), anti-La (SSB), anti-ribonucleoprotein (RNP) and anti-phospholipid antibodies, rheumatoid factor (RF) and anti-citrullinated peptide antibodies (ACPA) (if present) by visit. Time frame: baseline, and follow-up visits of the core study period at Week 3, 5, 7, 9, 12, 16, 20, 24, 28, 32, 36, and at Week 42, 48, 54, 60, 66, 72, 78 and 84 of the LTE observational period.
- Change from baseline in serum complement factors for C3 and C4 by visit. Time frame: baseline, and follow-up visits of the core study period at Week 3, 5, 7, 9, 12, 16, 20, 24, 28, 32, 36, and at Week 42, 48, 54, 60, 66, 72, 78 and 84 of the LTE observational period.
- Change from Baseline in levels of protective vaccine-induced serum antibody titers for Tetanus toxoid, Diphtheria and Measles by visit. Time frame: baseline, and follow-up visits of the core study period at Week 3, 5, 7, 9, 12, 16, 20, 24, 28, 32, 36, and at Week 42, 48, 54, 60, 66, 72, 78 and 84 of the LTE observational period.

3. To evaluate whether daratumumab treatment is associated with clinical efficacy and glucocorticoid sparing, the following secondary outcome measures will be analyzed:

- Proportion of subjects with a SLE responder index of 4 (SRI-4), SRI-4 being defined as (1) a  $\geq 4$ -point reduction in SELENA-SLEDAI score as compared to baseline, and (2) no new BILAG A score or  $\leq 1$  new BILAG B score, and (3) no deterioration from baseline in the physician's global assessment by  $\geq 0.3$  points, at Week 12 (4 weeks after the last daratumumab injection). Time frame: Week 12.
- Proportion of subjects with a SLE responder index of 4 (SRI-4), SRI-4 being defined as (1) a  $\geq 4$ -point reduction in SELENA-SLEDAI score as compared to baseline, and (2) no new BILAG A score or  $\leq 1$  new BILAG B score, and (3) no deterioration from baseline in the physician's global assessment by  $\geq 0.3$  points, by visit. Time frame: baseline, and follow-up visits of the core study period at Week 3, 5, 7, 9, 12, 16, 20, 24, 28, 32, 36, and at Week 42, 48, 54, 60, 66, 72, 78 and 84 of the LTE observational period.

- Proportion of subjects that meet the Lupus Low Disease Activity State (LLDAS) response criteria by visit, time frame: up to Week 36. The LLDAS incorporates multiple measures of disease activity, such as: SLEDAI-2K  $\leq 4$ , with no activity in major organ systems (renal, CNS, cardiopulmonary, vasculitis, fever) and no hemolytic anemia or gastroenterological activity; no new features of lupus disease activity compared with the previous assessment; PGA (scale 0-3),  $\leq 1$ ; current prednisolone (or equivalent) dose  $\leq 7.5$  mg daily; well tolerated standard maintenance dose of immunosuppressive drugs and approved biologic agents, by visit. Time frame: baseline, and follow-up visits of the core study period at Week 3, 5, 7, 9, 12, 16, 20, 24, 28, 32, 36, and at Week 42, 48, 54, 60, 66, 72, 78 and 84 of the LTE observational period.
- Change from baseline in Systemic Lupus Erythematosus Disease Activity Index 2000 (SLEDAI-2K) scores by visit. Time frame: baseline, and follow-up visits of the core study period at Week 3, 5, 7, 9, 12, 16, 20, 24, 28, 32, 36, and at Week 42, 48, 54, 60, 66, 72, 78 and 84 of the LTE observational period.
- Change from baseline in physician global assessment (PGA), a scale ranging from 0-3, by visit, time frame: baseline, and follow-up visits of the core study period at Week 3, 5, 7, 9, 12, 16, 20, 24, 28, 32, 36, and at Week 42, 48, 54, 60, 66, 72, 78 and 84 of the LTE observational period.
- Change from baseline in CLASI (Cutaneous Lupus Erythematosus Disease Area and Severity Index), CDAI (Clinical Disease Activity Index) and proteinuria (urinary protein/creatinine ratio, UPCR) by visit. Time frame: baseline, and follow-up visits of the core study period at Week 3, 5, 7, 9, 12, 16, 20, 24, 28, 32, 36, and at Week 42, 48, 54, 60, 66, 72, 78 and 84 of the LTE observational period.
- Time to first flare (SELENA-SLEDAI flare index, SFI), SFI flare rates (mild/moderate or severe) were defined by the modified SELENA-SLEDAI SFI (the modified SFI excludes severe flares that were triggered only by an increase in the SELENA-SLEDAI score to  $>12$ ). Time frame: baseline, and follow-up visits of the core study period at Week 3, 5, 7, 9, 12, 16, 20, 24, 28, 32, 36, and at Week 42, 48, 54, 60, 66, 72, 78 and 84 of the LTE observational period.
- The daily prednisolone (or equivalent) dosage, by visit between Week 12 and Week 36. Time frame: baseline, and follow-up visits of the core study period at Week 3, 5, 7, 9, 12, 16, 20, 24, 28, 32, 36, and each follow-up visit of the LTE observational period.  
Time to new treatments to control lupus activity will be investigated. Time-frame: baseline, and follow-up visits of the core study period at Week 3, 5, 7, 9, 12, 16, 20, 24, 28, 32, 36, and at Week 42, 48, 54, 60, 66, 72, 78 and 84 of the LTE observational period.

4. To evaluate whether daratumumab treatment is associated with improvement of health-related quality of life, the following outcome measures will be performed:

- Change from baseline in Health-related quality of life (HR-QoL), measured by SF-36 score, time frame: up to Week 36. The 36-Item Short Form Health Survey questionnaire (SF-36), a validated instrument widely used to evaluate Health-Related Quality of Life SLE, by visit. Time frame: baseline, and follow-up visits of the core study period at Week 3, 5, 7, 9, 12, 16, 20, 24, 28, 32, 36, and at Week 42, 48, 54, 60, 66, 72, 78 and 84 of the LTE observational period.
- Change from baseline in Functional Assessment of Chronic Illness Therapy (FACIT)-Fatigue score. Time frame: up to Week 36. The FACIT-Fatigue scale includes 13-fatigue related questions for subject rates fatigue during the previous 7 days, yielding on overall score 0 to 52, with lowest score representing worst fatigue, by visit. Time frame: baseline, and follow-up

visits of the core study period at Week 3, 5, 7, 9, 12, 16, 20, 24, 28, 32, 36, and at Week 42, 48, 54, 60, 66, 72, 78 and 84 of the LTE observational period.

- Change from screening in the number of organs with damage according to the SLICC Damage Index (SDI) measured at the final visit at Week 84

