### 7.3.3 SLE RESPONDER INDEX (SRI-4)

The SRI-4 response is defined as  $\geq 4$ -point reduction from baseline in SLEDAI-2K score, no new BILAG A and no more than 1 new BILAG B domain score, and no worsening from baseline in the PGA ( $< 10\%$  worsening from baseline) [65]. For the endpoint analysis in this study, SRI-4 composite response is the proportion of subjects who achieve a SLEDAI-2K SRI-4 response at Week 3, 5, 7, 9, 12, 16, 20, 24, 28, 32, 36 of the core study period, and at Week 42, 48, 54, 60, 66, 72, 78 and 84 of the LTE observational period.

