#### 9.5.2 MAJOR SECONDARY ANALYSES

The number of participants is reported, who achieve a SLE responder index of 4 (SRI-4) upon daratumumab treatment at Week 12 (primary endpoint visit), i.e. 4 weeks after the last daratumumab injection. Descriptive statistics will be used to report the clinical efficacy parameters, the patient reported outcome measure SF-36 and serological efficacy parameters at each assessment. The change in efficacy parameters, patient reported outcomes will be calculated along with 95% confidence intervals.

Disease flares are defined by the SELENA-SLEDAI flare index. The time to flare during the study will be analyzed by Kaplan-Meier analyses. The need for next treatment to control the disease within the 6-months follow-up is also be analyzed by Kaplan-Meier analyses. The TEAE will be documented during daratumumab treatment. The incidence and the incidence rate per 10 treatment months of adverse events will be calculated. The incidence of serious adverse events will be separately reported.

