|------------------------------|------------------------------------------------------------------------------------------------------------------------|---|--------------------------|
| Proteinuria           | New onset or recent increase of more than 0,5mg/24hours.                                                               | 4 |  |
| Pyuria                | > 5 white blood cells/high field. Exclude infection.                                                                   | 4 |  |
| Rash                  | Ongoing inflammatory lupus rash.                                                                                       | 2 |  |
| Alopecia              | Ongoing abnormal, patchy or diffuse loss of hair.                                                                      | 2 |  |
| Mucosal ulcers        | Ongoing oral or nasal ulcerations.                                                                                     | 2 |  |
| Pleurisy              | Pleuritic chest pain with pleural rub or effusion, or pleural thickening.                                              | 2 |  |
| Pericarditis          | Pericardial pain with at least 1 of the following: rub, effusion, or electrocardiogram or echocardiogram confirmation. | 2 |  |
| Low complement        | Decrease in CH50, C3, or C4 below the lower limit of normal for testing laboratory.                                    | 2 |  |
| Increased DNA binding | Increased DNA binding by Farr assay above normal range for testing laboratory.                                         | 2 |  |
| Fever                 | >38°C. Exclude exclude infectious cause.                                                                               | 1 |  |
| Thrombopenia          | <100,000 platelets / x 10  /L, exclude drug causes                                                         | 1 |  |
| Leukopenia            | <3,000 white blood cells / x 10  /L, exclude drug causes                                                   | 1 |  |

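### SRI-4 is defined differently in sections 3.2.3 and 7.3.3: the BILAG criterion uses 'or' in one and 'and' in the other, and the PGA limit and index name do not match

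*Protocol*

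**What the plan says.** The protocol defines SRI-4 in two places that cover the same visits, Week 12 included.

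- **Section 3.2.3** (item 3, worded identically for Week 12 and by visit) requires a 4-point or larger "reduction in SELENA-SLEDAI score as compared to baseline, and (2) no new BILAG A score or" at most one new BILAG B. Its third condition is "no deterioration from baseline in the physician's global assessment by" 0.3 points or more.
- **Section 7.3.3** requires a 4-point or larger fall in SLEDAI-2K, with "no new BILAG A and no more than 1 new BILAG B domain score, and no worsening from baseline in the PGA", the last condition glossed as less than 10% worsening from baseline. It then names the SLEDAI-2K version as the one used for the endpoint analysis.

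Section 9.5.2 opens the major secondary analyses with this endpoint at Week 12: "The number of participants is reported, who achieve a SLE responder index of 4 (SRI-4"). It does not say which definition applies. The synopsis lists SRI-4 without defining it.

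**The concern.** One endpoint has two operative definitions that differ on three elements: the index, the logical connector in the BILAG condition, and the PGA limit. If the differences change who is classed as a responder, the protocol does not determine the Week 12 count uniquely. The trial is open-label and uncontrolled, so blinding would not protect a choice of definition made once results are known. A statistical analysis plan, not seen here, may settle the matter, but the two protocol texts would still disagree.

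**Working it through.** The protocol gives no numerical figure for SRI-4 to reproduce; the sample size rests on anti-dsDNA. The check applies both definitions as logical rules.

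**Inputs.** Section 3.2.3: new A = 0 *or* new B ≤ 1; PGA rise < 0.3 points. Section 7.3.3: new A = 0 *and* new B ≤ 1; PGA worsening < 10% from baseline. Section 7.2.9: PGA scale 0 to 3. Section 9.2: 10 patients.

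**Step 1, BILAG.** Result for each combination of new scores:

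| New A | New B | 3.2.3 (or) | 7.3.3 (and) |
|---|---|---|---|
| 0 | 0 or 1 | pass | pass |
| 0 | 2 or more | pass | **fail** |
| 1 or more | 0 or 1 | pass | **fail** |
| 1 or more | 2 or more | fail | fail |

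The rules disagree in two of the four rows, each time with 3.2.3 the more lenient. The no-worsening rules in sections 7.2.4 and 7.3.5 also use *and*, so section 3.2.3 stands alone.

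**Step 2, PGA.** Reading 7.3.3 literally, as 10% of the patient's own baseline, the permitted rise is less than 0.10 × baseline:

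| Baseline PGA | 7.3.3 limit | 3.2.3 limit |
|---|---|---|
| 1.0 | 0.10 | 0.30 |
| 1.5 | 0.15 | 0.30 |
| 2.0 | 0.20 | 0.30 |
| 2.5 | 0.25 | 0.30 |
| 3.0 | 0.30 | 0.30 |

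For example, a rise from 1.5 to 1.7 is 0.2 points, which passes 3.2.3. As a percentage it is 0.2 / 1.5 = 13.3%, which fails 7.3.3.

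In 0.1-point steps, with baselines 0.1 to 3.0 and follow-up values 0 to 3.0, there are 30 × 31 = 930 pairs. The rules disagree in 30 of them: a rise of 0.1 from a baseline of 1.0 or below (10 pairs) and a rise of 0.2 from a baseline of 2.0 or below (20 pairs). All 30 pass 3.2.3 and fail 7.3.3, and none goes the other way. This maps where the rules differ; it is not a probability.

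On the alternative reading, 10% of the scale length is 0.10 × 3 = 0.3 points, and the two rules are identical.

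**Step 3, index.** Both study schedules (core and extension) and Attachment B provide SLEDAI-2K only; no separate SELENA-SLEDAI score is scheduled or attached.

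**Step 4, size.** One patient of 10 is 1/10 = 10 percentage points of the response rate.

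**Step 5, serology items.** On the Attachment B form, increased DNA binding scores 2 points and low complement ("Decrease in CH50, C3, or C4 below the lower limit of normal for testing laboratory") scores 2. Together they give 2 + 2 = 4, the whole SRI-4 threshold.

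**The case against.** The strongest reply is that the intended definition is not in real doubt. Section 7.3.3 sits under the efficacy endpoint definitions and names the SLEDAI-2K version for the analysis. Every other BILAG no-worsening rule uses *and*, so the *or* in 3.2.3 looks like a drafting slip copied once. The endpoint is secondary, descriptive and reported as a count. Much of this stands, and it limits the point in these ways:

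- **Index.** A reader might infer that two different scores compete. The documents do not support that: only one score is collected, and the protocol also derives its SELENA-SLEDAI flare index from SLEDAI-2K (sections 7.2.3 and 7.3.4). SELENA-SLEDAI scoring is not described, so reclassification through the index cannot be shown. It is a naming conflict.
- **PGA.** A reader might call the two limits incompatible. They are incompatible only if 10% refers to the patient's baseline. That is the more literal reading, but the scale-length reading makes them agree. It is an ambiguity.
- **Severe flares counted as responders.** This might be inferred from the *or*, but the protocol does not equate a new BILAG A with a severe flare; section 7.3.4 defines severe flare through the flare index. Such a patient would also need the 4-point SLEDAI fall and the PGA condition.
- **Serology alone producing response.** This is possible but is not an error in the plan. It needs low complement at baseline, which is not an entry criterion, and normalisation of both items, whereas section 9.2 plans on an anti-dsDNA reduction of about 50%. Entry positivity is by ELISA while the form scores DNA binding by Farr assay, so entry does not guarantee the 2 points. Serology and several clinical measures are also reported separately by visit.

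The BILAG conflict survives the reply. Calling the *or* a slip concedes that the formal endpoint definition, stated twice, is wrong as written.

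**Conclusion.** The point holds as an inconsistency that should be fixed. The BILAG connector in section 3.2.3 is a clear error: read as written, it admits patients whom sections 7.3.3, 7.2.4 and 7.3.5 would count as worsened. The PGA limit is ambiguous and the index is misnamed.

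On BILAG and PGA, following 3.2.3 can only keep or raise the response rate, by 10 percentage points for each reclassified patient if all 10 are in the denominator. The documents give no basis for estimating how many patients would be affected, and the number could be zero.

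The consequence is confined to a descriptive secondary endpoint. It would be too strong to call SRI-4 the trial's headline result: it is the first clinical efficacy measure listed, but it follows safety and serology. The anti-dsDNA primary endpoint, the sample size and the safety review do not depend on it.

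**What to change.** Use one definition in section 3.2.3 (both bullets) and section 7.3.3: a SLEDAI-2K reduction of at least 4 points from baseline, AND no new BILAG A, AND at most one new BILAG B, AND a PGA increase below 0.3 points on the 0-3 scale (10% of the scale). This follows 7.3.3 for the index and connector and 3.2.3 for the PGA limit. It should be settled before the SRI-4 data are analysed.

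The cost is a short text correction. All components are already collected at the relevant visits, and no visit, assessment or sample-size figure changes.

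Optionally, and not as a correction, add one supplementary row giving SRI-4 computed without the anti-dsDNA and complement items. It would show whether any response rests on those items alone. Inclusion criterion 5 already uses a related clinical SLEDAI-2K, although that version excludes all laboratory results.

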## Time and events schedule

### 1. Study procedures of the core study period

|                                                   | Screening | Baseline |          |    |    |    |    |    |    |    | Primary
Endpoint |         |     |     |     |     | End of core
study period |
|---------------------------------------------------|-----------|----------|----------|----|----|----|----|----|----|----|---------------------|---------|-----|-----|-----|-----|-----------------------------|
| Week                                              |           | 1        | 2        | 3  | 4  | 5  | 6  | 7  | 8  | 9  | 12                  | 16      | 20  | 24  | 28  | 32  | 36                          |
| Days                                              | 28-1d     | 0        | 7        | 14 | 21 | 28 | 35 | 42 | 49 | 56 | 77                  | 105     | 133 | 161 | 189 | 217 | 241                         |
| Time window                                       |           |          | +/- 1 d* |    |    |    |    |    |    |    | +/- 3 days          | +/- 7 d |     |     |     |     | +/- 7 d                     |
| Study visits                                      | 1         | 2        | 3        | 4  | 5  | 6  | 7  | 8  | 9  | 10 | 11                  | 12      | 13  | 14  | 15  | 16  | 17                          |
| Screening / Administrative                        |           |          |          |    |    |    |    |    |    |    |                     |         |     |     |     |     |                             |
| Informed consent/assent (ICF)                     | x         |          |          |    |    |    |    |    |    |    |                     |         |     |     |     |     |                             |
| Demographics                                      | x         |          |          |    |    |    |    |    |    |    |                     |         |     |     |     |     |                             |
| Review medical history requirements               | x         |          |          |    |    |    |    |    |    |    |                     |         |     |     |     |     |                             |
| Inclusion/exclusion criteria                      | x         | x        |          |    |    |    |    |    |    |    |                     |         |     |     |     |     |                             |

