### 4.2 OVERVIEW OF STUDY DESIGN

After a screening period of 4 weeks, the following visits are planned in the core study period:

[figure not shown]

The long-term extension observational period includes a total of 8 follow-up visits every 6 weeks as follows:

[figure not shown]

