#### 6.4.1 GLUCOCORTICOID THERAPY

The use of glucocorticoids for the indication SLE is allowed to a maximum of 20mg daily prednisolone (or equivalent) throughout the study. The glucocorticoid dosage must be stable from baseline until Week 12 (primary endpoint study visit). After Week 12 (primary endpoint visit), it is possible to reduce the glucocorticoid dosage if the disease activity allows tapering, according to the judgment of the treating physician.

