### 6.5 RESCUE MEDICATION

For the treatment of disease flares, defined according to the SLEDAI-flare index (SFI), administration of glucocorticoids is allowed up to a maximum dose of 100mg/day. In case of recurring flares or ongoing disease activity, defined as a state of not achieving low disease-activity (LLDAS), administration of additional disease-modifying drugs is allowed from Week 12 (primary endpoint visit) (except for medications listed in section 6.6 PROHIBITED THERAPIES).

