## 6.6 PROHIBITED THERAPIES

Use of additional immunosuppressants or immunomodulators, other than those explicitly allowed in the inclusion/exclusion criteria are prohibited including, but not limited to, the following:

- Agents targeted at reducing TNF (e.g. infliximab, golimumab, certolizumab pegol, etanercept, and adalimumab)
- B-cell depleting agents (e.g. rituximab, obinutuzumab or ocrelizumab)
- Interleukin-1 inhibitors (e.g. canakinumab)
- IL-1 receptor antagonist (e.g. anakinra)
- Interleukin-2 inhibitors or exogenous IL-2 therapy
- Tocilizumab or any other biologic targeting IL-6 or IL-6 receptor
- Tofacitinib, baricitinib, filgotinib, upadacitinib or any other janus kinase (JAK) inhibitors
- Abatacept
- Anti-IL-17 agents (e.g. secukinumab or ixekizumab)
- Anti-IL-23 agents (e.g. guselkumab)
- Leflunomide
- Tacrolimus or other immunomodulatory oral or topical preparations
- Thalidomide or lenalidomide
- Dapsone

Use of cytotoxic drugs is prohibited including, but not limited to, cyclophosphamide, chlorambucil, nitrogen mustard, or other alkylating agents. Multiple administrations of high doses of oral glucocorticoids (average daily dose  $\geq 20$  mg), or initiation of high potency topical glucocorticoids, are prohibited during the study. Sulfa-based antibiotics, where reasonable, should generally be avoided. The use of complementary therapies (e.g. herbs, ointments, traditional Chinese medicine, and acupuncture) that have the potential to activate or inhibit the immune system is prohibited. In addition, use of complementary therapies that have the potential to interact with antithrombotic agents is prohibited in those taking antithrombotic agents. The use of other complementary therapies is strongly discouraged; in individual cases, use may be permitted following discussion with the study sponsor and/or medical monitor.

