### 7.3.7 GLUCOCORTICOID DOSAGE

In this study, tapering of the glucocorticoid dosage administered for the indication SLE is allowed after Week 12 (primary end point visit), if justified according to the judgment of the treating physician (See section 6.4.1 GLUCOCORTICOID THERAPY). This allows investigating the steroid sparing effect of the study drug, and steroid reduction is one of the secondary endpoints, as advocated by leading experts in managing lupus [83]. The glucocorticoid dosage must be stable until Week 12 and may be tapered thereafter. The average reduction of oral glucocorticoid will be analyzed at baseline, and follow-up visits of the core study period at Week 3, 5, 7, 9, 12, 16, 20, 24, 28, 32 and 36, and Week 42, 48, 54, 60, 66, 72, 78 and 84 of the LTE observational period.

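### The glucocorticoid endpoint is a dose by visit, limited to oral steroid in Section 7.3.7, so parenteral rescue and oral courses completed between visits are not counted

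*Protocol*

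**What the plan says.** The endpoint is described in two places that do not match on route. Section 3.2.3 (and the synopsis) gives "The daily prednisolone (or equivalent) dosage, by visit between Week 12 and Week 36", with the extension visits added and no restriction on route. Section 7.3.7 says "The average reduction of oral glucocorticoid will be analyzed at baseline, and follow-up visits of the core study period", so there it is oral only. The same section gives the endpoint its purpose: "This allows investigating the steroid sparing effect of the study drug, and steroid reduction is one of the secondary endpoints".

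Steroid use is governed by three further passages:
- Section 6.4.1: "The use of glucocorticoids for the indication SLE is allowed to a maximum of 20mg daily prednisolone (or equivalent) throughout the study".
- Section 6.5, for flares meeting the SFI: "administration of glucocorticoids is allowed up to a maximum dose of 100mg/day". No route, course length or link to visits is given.
- Section 6.6 prohibits "Multiple administrations of high doses of oral glucocorticoids (average daily dose" of 20 mg or more).

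The core schedule puts the visits from Week 20 to Week 36 on Days "133 | 161 | 189 | 217 | 241", after Week 12 on Day 77 and Week 16 on Day 105. For the extension, Section 4.2 states: "The long-term extension observational period includes a total of 8 follow-up visits every 6 weeks as follows".

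No passage says how a rescue course enters the glucocorticoid endpoint.

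**The concern.** A flare course is steroid given for SLE, so it belongs in any measure of steroid sparing. An endpoint that takes the dose at scheduled visits, and by 7.3.7 only the oral dose, can miss it in two ways. A parenteral course is excluded by definition. An oral course that starts and ends between two visits leaves no trace in the dose at either visit. Both omissions fall on patients who flared, and both make their reported exposure too low. With 10 patients and no control arm, one or two such courses can matter to the reported dose curve for an interval.

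**Working it through.** The protocol gives no expected steroid reduction, so there is no stated figure to reproduce. The check uses the visit schedule with assumed doses.

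**Visit gaps.** Days 77, 105, 133, 161, 189, 217 and 241 give gaps of 28, 28, 28, 28, 28 and 24 days, in total 241 − 77 = 164 days. Extension gaps are 6 × 7 = 42 days. A one- or two-week course fits inside any of them.

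**Illustrative patient (assumed doses).** Baseline 10 mg; 5 mg at Weeks 16 and 20. Between those visits a flare is treated with 50 mg for 7 days and 30 mg for 7 days, followed by 5 mg for 14 days.
- By-visit dose: 5 mg at both visits, a 50% reduction from baseline.
- Mean over the 28 days: (50×7 + 30×7 + 5×14)/28 = 630/28 = 22.5 mg/day.
- Mean over Week 12 to 36, with 5 mg on all other days: 5 + (45×7 + 25×7)/164 = 5 + 490/164 ≈ 8.0 mg/day, a 20% reduction.
- If 10 mg is instead kept until Week 16: (10×28 + 630 + 5×108)/164 = 1450/164 ≈ 8.8 mg/day, about a 12% reduction.
- Effect on a mean over 10 patients: (22.5 − 5)/10 = 1.75 mg/day for that interval, and (8.0 − 5)/10 = 0.3 mg/day over the whole period.

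**Range.** For a period of T days, background dose p, and a rescue dose R for k days, the mean is [(T − k)p + kR]/T. With an assumed taper from 10 to 7.5 mg, the by-visit change is −2.5 mg/day in every row below. The cells show the time-averaged change from baseline in mg/day.

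| Course | 28-day gap | 42-day gap | Week 12–36 (164 days) |
|---|---|---|---|
| 40 mg × 3 days | +0.98 | −0.18 | −1.91 |
| 40 mg × 7 days | +5.62 | +2.92 | −1.11 |
| 100 mg × 3 days | +7.41 | +4.11 | −0.81 |
| 100 mg × 7 days | +20.62 | +12.92 | +1.45 |

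Within a single gap the apparent reduction often becomes an increase. Over the full period it usually shrinks without changing sign. With a deeper taper (10 to 5 mg), a 40 mg × 3-day course does not reverse the sign even in a 28-day gap: the mean is 8.75 mg, a change of −1.25.

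**Direction for oral courses.** If the second visit of the illustrative patient fell on a random day of the 28, the recorded dose would have expectation 50×7/28 + 30×7/28 + 5×14/28 = 22.5 mg, equal to the true mean. When course timing is unrelated to visits, a visit dose is therefore noisy and not systematically low. A parenteral course under 7.3.7 is missed whatever day the visit falls on.

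**The case against.** The strongest reply has four parts.

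- **Visit day is not a quotation.** The protocol reports nearly every secondary endpoint by visit, and average reduction in 7.3.7 is undefined. An SAP that is not at hand could define a dose window. This stands in part: visit-day dose is the plainest reading, not a stated rule. The restriction to oral steroid, however, is written in 7.3.7, and an SAP that counted parenteral steroid would depart from it.
- **Oral timing adds noise more than bias.** This stands, as the random-visit calculation shows. A visit during an oral course would overstate exposure for the interval. Only the loss of parenteral courses is certain to be one-sided.
- **Rescue use is visible elsewhere.** A prednisone increase for SLE activity is a flare criterion (7.3.4), time to flare is analysed by Kaplan-Meier (9.5.2), and patients with medication increases are listed (9.1.6). With 10 patients each case can be found. This stands, but none of these outputs corrects the reported dose.
- **The study is exploratory.** The analysis is descriptive and uncontrolled, which limits the consequence but does not make the measure right.

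A reader might go further and infer that a patient who needed more steroid will be reported as steroid-spared, or that the endpoint always errs in favour of the drug. The documents support neither. No steroid-spared category exists, because the endpoint is a continuous dose. The illustrative patient averages about 8.0 mg/day over Week 12 to 36, which is still below the 10 mg baseline.

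**Conclusion.** The point holds in a limited form. Sections 3.2.3 and 7.3.7 disagree on route, and neither says how rescue steroid enters the endpoint. Parenteral rescue is left out one-sidedly under 7.3.7, and an oral course completed between visits is not counted on the plainest reading of the text. The reported dose can then understate exposure in patients who flared: 5 mg against 22.5 mg/day within one 28-day interval, and a 50% against a 20% reduction over Week 12 to 36. These sizes rest on assumed doses and course lengths, and on the course falling between visits. How often this would happen cannot be judged from the protocol. The primary endpoint is not touched. What is affected is the interpretation of a named secondary endpoint.

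**What to change.** - Align Sections 3.2.3 and 7.3.7 on route.
- Alongside the by-visit dose, report the mean daily prednisolone-equivalent dose of all systemic glucocorticoid given for SLE since the previous visit, rescue included. Keeping the SLE indication, as 7.3.7 does, leaves out the pre- and post-dose steroid of Sections 6.2.2 and 6.2.3.
- Add the cumulative dose for Week 12 to 36 and for Week 36 to 84.
- Derive these from the concomitant-therapy record, and confirm that the CRF captures dose, route and start and stop dates. The protocol schedules a concomitant-therapy review at each visit but does not expressly say that these details are recorded for steroids.
- Reconcile the 20 mg maximum in 6.4.1, the limit on high average oral doses in 6.6 and the 100 mg/day allowance in 6.5, since together they determine which courses count as permitted.

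The cost is revised endpoint wording and a short derivation. If the CRF lacks dose or dates, steroid entries would also have to be completed from source records.
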